## Abstract

**Background**: Postoperative hypotension associated with postoperative morbidity and early mortality has been studied previously. Hypertension and other hemodynamic, respiratory, and temperature abnormalities have comparatively understudied during the first postoperative days.

**Methods**: This bi-centre observational cohort study will include 114 adult patients undergoing non-cardiac surgery hospitalized on an unmonitored general care floor and wearing a multi-signal wearable sensor, allowing remote monitoring (
Biobeat Technologies Ltd, Petah Tikva, Israel). The study will cover the first 72 hours after discharge of the patient from the post-anaesthesia care unit. Several thresholds will be used for each variable
(arterial pressure, heart rate, respiratory rate, oxygen saturation, and skin temperature). Data obtained using the sensor will be compared to data obtained during the routine nurse follow-up. The primary outcome is hemodynamic abnormality. The secondary outcomes are postoperative respiratory and temperature abnormalities, artefacts and blank/null outputs from the wearable device, postoperative complications, and finally, the ease of use of the device. We hypothesize that remote monitoring will detect abnormalities in vital signs more often or more quickly than the detection by nurses’ routine surveillance.

**Discussion**: A demonstration of the ability of wireless sensors to outperform standard monitoring techniques paves the way for the creation of a loop which includes this monitoring mode, the automated creation of alerts, and the sending of these alerts to caregivers.

**Trial registration**: ClinicalTrials.gov,
NCT04585178. Registered on October 14, 2020

## Introduction

Postoperative mortality remains a current controversial issue, as shown in 2016 by the International Surgical Outcomes Study.
^
1
^ This prospective international cohort study reported that 16.8% of patients developed one or more postoperative complications, and 0.5% died. Several studies have focused specifically on the risks of postoperative hypotension,
^
2
^ respiratory depression,
^
3
^ and hypoxemia.
^
4
^ This has been well demonstrated in particular with regard to unrecognized hypotension since the risk of myocardial ischemia is increased by cumulative durations of 2 to 4 h of hypotension (mean arterial pressure < 60 mmHg) or durations of more than 4 h with mean arterial pressure < 65 or 70 mmHg.
^
5
^

Most patients are hospitalized on an unmonitored general care floor (ward) where survival after a cardiac arrest is worse compared to ICU patients or patients hospitalized in a monitored ward setting.
^
6
^ However, postoperative placement in high-level monitoring units for patients with risk factors is impossible in view of their number. To limit the risk of missing an abnormality in one of the physiological parameters, the National Health Service in England proposed (imposed in fact) a rigorous and repeated evaluation of the clinical condition at regular intervals with early warning scores (EWS).
^
7
^ But this evolution in nursing practice does not prevent it from being spot check monitoring. Evolution of technology allows continuous and remote monitoring using either a bed-based mattress sensor, patient-worn monitor, and wearable patch sensors allowing continuous monitoring.

The most convenient system for patients, which makes them fully independent and therefore does not impede their mobility, is a skin patch that measures a wide range of vital signs at a frequent rate and automatically transmits this information to the nursing staff. Remote wireless vital sign monitoring on the ward has been reported in case series of medical or surgical patients
^
8
^ and more recently in patients suffering from COVID-19.
^
9
^

To promote the widespread use of these devices, it is necessary to confirm the comparative advantage of remote monitoring over conventional nursing monitoring. In the present study, we hypothesize that monitoring with a multi-signal wearable sensor will detect potentially dangerous vital sign abnormalities more often and more rapidly than routine surveillance in surgical patients hospitalized on an unmonitored general care floor. Data obtained using the sensor will be compared to data obtained during the routine nurse follow-up during at most 72 first postoperative hours.

## Methods

Ethics approval for this trial was obtained from the Ethical Committee Ile de France II (Paris, France) on September 28, 2020 (approval number: 2020-A01852-37) and registered at
ClinicalTrials.gov under the trial identification number NCT04585178).

Written informed consent will be obtained by study staff from all study participants prior to their participation in study. Any modifications to the protocol will be sent to the Ethical Committee before they are implemented within the study and communication changes that impact the patients would require signing of a revised consent form. The current version is version n° 2; July 28; 2020. Complete protocol can be obtained on request. The study protocol has been reported in accordance with the Standard Protocol Items: Recommendation for Clinical Interventional Trials (SPIRIT) guidelines.

### Aim, study design and setting

This protocol seeks to quantify the benefit of remote monitoring using a multiparametric device in the detection of postoperative complications in comparison with the monitoring usually performed by nurses.

The Biobeat-Postop Protocol is a prospective observational bi-centre study that will be conducted in two private non-profit hospitals in which all types of surgical procedures, except cardiac procedures, are routinely performed. Patients will be consecutively enrolled and followed up for the first 72 postoperative hours after the patient leaves the post-anaesthesia care unit.

Recruitment of patients began on December 15, 2020, and is ongoing.

### Study population and eligibility criteria

Patients will be included if they meet the following criteria: (1) are over 18 years, (2) require general anaesthesia for a major surgical procedure (gastro-intestinal surgery, gynaecological surgery, urologic surgery, and orthopaedic surgery) with an expected duration of intervention of more than 2 hours, (3) need a planned postoperative stay of more than 72 hours, and (4) have provided written informed consent. The exclusion criteria will be any abnormality of the skin or a very hairy skin at the location of the patch, tremor, allergy to the components of the patch, planned scanner or magnetic resonance imaging during the postoperative course, and pregnancy. Consecutive patients will be screened unless the physician responsible for providing the patient information and consent is not available in accordance with the regulations.

### The studied device

Patients will be equipped with a portable Biobeat
^®^ sensor, a single-use patient device that consists of a skin patch placed 1 cm to the left of the sternum, just below the clavicle (
Biobeat Technologies Ltd, Petah Tikva, Israel) (
Figure 1). The sensor continuously records the photoplethysmographic waveform, which allows recording and calculation of several physiological parameters: heart rate (HR), respiratory rate (RR), peripheral oxygen saturation (SpO
_2_), systolic arterial pressure (SAP) and SAP variation, diastolic arterial pressure (DAP) and DAP variation, and skin temperature. Other variables, stroke volume and cardiac output, are measured by this sensor but are not included in this protocol.

**Figure 1. f1:**
[figure not shown]
The sensor and placement of the patch sensor (consent obtained for publication).

Biobeat
^®^ is CE approved (N°688840; March 19, 2019), and its use was also approved by the FDA in 2019 (510K clearance for measurement of arterial pressure, oxygenation and HR in hospitals, clinics, and long-term care and at home).

High agreement has been demonstrated for arterial pressure measurements obtained via the Biobeat
^®^ sensor and the gold-standard sphygmomanometer technique.
^
10
^

### Procedure

Patient selection will be performed during a preoperative anaesthesia consultation with one of the doctors on the research team. After verification of the inclusion and exclusion criteria, the physician will inform the patients about the study and obtain their written informed consent.

The patch will be put in place in the post-anaesthesia care unit just before the patient's return to the conventional hospitalization service. The monitoring data from the patch will be recorded continuously without being communicated to the nursing staff and doctors.

Postoperative medical, surgical, and nursing care will be in accordance with medical indications depending on the clinical routine, without any study-specific restrictions, and all the nurses’ observations (clinical observations and measurements) will be noted on a computerized chart (
Easily) as usual.

Data collection will end 72 hours after the patient's return to the hospital ward. Finally, when a nurse removes the patch, the status of the skin will be assessed: healthy skin (stage 0), redness limited to the contact area between the device and the skin (stage 1), redness extending beyond the contact surface of the device (stage 2), and the appearance of blisters (stage 3). The patients will be asked to evaluate their acceptance of the sensor using a 4-point Likert scale (from 0 = intolerable to 4 = no problem at all).
^
11
^

Safety assessments will consist of monitoring and recording of all adverse events.

Any participant who wishes to terminate their participation in the study can withdraw from the trial at any time without the need for further explanation. Participants who withdraw from the study will be followed up according to routine clinical practice.

Otherwise, patients will be excluded during the study if they must undergo an unplanned scan or magnetic resonance imaging during the period of monitoring. In this case, the patch will be removed before the radiologic examination.

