### Outcome measures

The main outcome is the occurrence of one or more episodes with a mean arterial pressure below the threshold of 60 mmHg during the first 72 hours following a major non-cardiac surgical procedure unless death or hospital discharge occurs sooner, with the 72-hour period starting when the patient returns to the surgical department. The secondary outcomes will concern the frequency of postoperative respiratory or temperature abnormalities and their duration, the frequency of artefacts and blank/null outputs from the wearable device and, more globally, the signal-level validity, the postoperative complications that occurred during the monitoring period, as determined by the healthcare team in accordance with the Dindo and Clavien classification
^
12
^ and the comprehensive complication index.
^
13
^ Finally, the ease of use of the device at the time of insertion and the patient’s tolerance to wearing the Biobeat
^®^ device will also be determined. Definitions of hemodynamic, respiratory, and temperature abnormalities are listed in
Table 1.

**Table 1. T1:** Outcome definitions.

Primary Outcome Measure
Postoperative haemodynamic abnormality
• a MAP < 70 mmHg
• or a MAP < 65 mmHg
• or a MAP < 60 mmHg
• or a MAP < 80% of the value measured during the pre-anaesthesia consultation
• or a MAP < 70% of the value measured during the pre-anaesthesia consultation
• or a MAP < 80% of the value measured in the OR before the induction of anaesthesia
• or a MAP < 70% of the MAP measured in the OR before the induction of anaesthesia
• or a MAP > 100 mmHg
• or a MAP > 110 mmHg
• or a MAP > 120 mmHg
• or a MAP > 130 mmHg
• or a MAP > 120% of the MAP measured during the pre-anaesthesia consultation
• or a MAP > 130% of the MAP measured during the pre-anaesthesia consultation
• or a MAP > 120% of the MAP measured in the OR before induction of anaesthesia
• or a MAP > 130% of the MAP measured in the OR before induction of anaesthesia
• or a heart rate < 40/min
• or a heart rate > 100/min
• or a rhythm disorder
Secondary Outcomes
Postoperative respiratory abnormality
• breathing rate < 8/min
• breathing rate > 20/min
• or a peripheral oxygen saturation < 95%
• or a peripheral oxygen saturation ≤ 92%
• or a peripheral oxygen saturation ≤ 90%
• or a peripheral oxygen saturation ≤ 85%
Postoperative temperature abnormality
• a temperature ≤ 36.8°C
• or a temperature ≥ 38°C
• or a temperature ≥ 39°C

MAP: mean arterial pressure; OR.

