### Statistics

Sample size

Our main goal is to estimate the proportion of patients showing severe hypotension and, notably, to corroborate the prevalence found in Liem
*et al.*
^
5
^
*i.e.*, 8%. To gain a 10% precision (± 5%) with a two-sided 5% alpha risk, 114 patients need to be included.

Detection of artefacts

This will follow similar rules as previously published in a paper dedicated to the validation a new sensor.
^
14
^ The rules selected to define artefacts may be updated according to experience and the literature.
^
15
^ The successive rules will be recorded in a register, and all recordings will be reviewed in the light of these new rules.

Missing values

Missing data will not be replaced.

Statistical analyses

Descriptive summaries will be provided for each parameter and for each device. For continuous variables, the mean, median, and their 95% confidence limits, obtained using bootstrapping methods, will be provided. For discrete variables, counts, percentages, and confidence limits obtained using a bootstrap method will be provided
*.*

The proportion of data gaps and artefacts for each parameter will be given as a percentage of the total number of measurement points and observations, respectively, with the corresponding 95% confidence interval (CI).

When physiologic parameters (HR, SAP, DAP, for instance) are measured simultaneously by nurses and wearable devices, a Bland-Altman analysis for repeated measurements, accounting for multiple observations per individual, will be performed to draw mean-difference plots and derive accuracy or bias (mean difference), precision (standard deviation of difference), and limits of agreement (LoAs) that are expected to contain 95% of the paired differences between measurements by the nurses and the wireless patch, with their confidence intervals.

At the patient level and for each kind of clinical event, the proportion of patients with detection of at least one event (hypotension, for instance) by a nurse and wearable monitoring will be described in a two-by-two table. Agreement will be estimated by Cohen’s kappa coefficient with its 95% CI, while differences will be tested by a non-parametric McNemar test for paired nominal data.

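### The patch-acceptance scale is called 4-point but runs from 0 to 4, and patients who stop because of the patch may go unscored, so tolerance may be overstated

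*Protocol article*

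**What the plan says.** The Procedure section of the protocol article sets two measures for the end of wear. The first is the skin: "when a nurse removes the patch, the status of the skin will be assessed", in four stages numbered 0 to 3. The next sentence has patients rate their acceptance of the sensor "using a 4-point Likert scale (from 0 = intolerable to 4 = no problem at all"). Both follow the statement that data collection ends 72 hours after return to the ward. Outcome measures lists the patient's "tolerance to wearing the Biobeat" device among the secondary outcomes.

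The same Procedure section lets any participant "withdraw from the trial at any time without the need for further explanation". It then says: "Participants who withdraw from the study will be followed up according to routine clinical practice". Patients who need an unplanned scan or magnetic resonance imaging are excluded during the study and have the patch taken off first. Under Statistics, the rule on missing values is one sentence: "Missing data will not be replaced".

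**The concern.** There are two separate problems.

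The first is a plain contradiction. A scale scored from 0 to 4 is not a four-point scale, and the article does not show whether the label or the upper anchor is wrong. The intermediate levels have no labels. A published mean or distribution could not be interpreted with confidence: a score of 3 is the best possible answer on a 0 to 3 scale and one step short of it on a 0 to 4 scale.

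The second is a gap in who gets scored. The patient for whom the patch was unbearable is the clearest negative result this outcome can have. That patient is also the one most likely to stop early, perhaps by pulling the patch off, and need give no reason. If no score is taken at that point, the patient leaves the tolerance figure, and the loss can only flatter the device. The skin stage is exposed to the same loss, and it is the only device-related harm for which the article gives a grading.

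**Working it through.** **1. Count of scale levels.** The inputs are the lower anchor 0 and upper anchor 4 (Procedure). Number of integer scores = 4 − 0 + 1 = 5. The label says 4. A four-level scale would have to run 0 to 3 or 1 to 4, and neither matches the printed anchors. The skin scale in the same paragraph is consistent: 3 − 0 + 1 = 4 stages.

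**2. The denominator.** The only sample-size figure in the article is 114: "To gain a 10% precision (± 5%) with a two-sided 5% alpha risk, 114 patients need to be included". With p = 0.08 and half-width d = 0.05, n = 1.96² × 0.08 × 0.92 / 0.05² = 113.09, which rounds up to 114. The stated figure is reproduced. It is used below only as the number of patients wearing a patch, and this point does not affect it.

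**3. Which early removals the text covers.**

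- A nurse removes the patch early: the skin check applies as worded, and the acceptance question follows it. Neither is limited to patients who complete 72 hours.
- The patient removes the patch: this falls outside the wording, which depends on a nurse doing so.
- Withdrawal: the text mentions neither a final score nor a recorded reason, only routine follow-up.
- Imaging: removal is described, but no skin stage or score is mentioned. These removals are not caused by intolerance, so they do not bias the result in the same way.

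**4. What unscored removals could do.** Let N = 114, b = patients scoring 0 among those scored, and w = patients who stop for intolerance and go unscored, with everyone else scored. Then:

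- reported share intolerable = b / (N − w)
- share in all patients = (b + w) / N

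The article gives no withdrawal rate, no reasons and no score distribution, so b = 2 and w = 0 to 10 are assumptions.

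| w (assumed) | Reported | All patients | Understated by |
|---|---|---|---|
| 0 | 2/114 = 1.8% | 2/114 = 1.8% | 0 points |
| 2 | 2/112 = 1.8% | 4/114 = 3.5% | 1.7 points |
| 5 | 2/109 = 1.8% | 7/114 = 6.1% | 4.3 points |
| 10 | 2/104 = 1.9% | 12/114 = 10.5% | 8.6 points |

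The mean score moves less. If scored patients average 3.5 (assumed) and the unscored would have given 0, the mean is too high by 3.5 × w / 114. That is 0, 0.06, 0.15 and 0.31 points for w = 0, 2, 5 and 10. If the score is taken at early removal, w = 0 and there is no bias.

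**The case against.** The case against accepts the scale error and disputes most of what might be built on it.

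- **Pooling.** A reader might infer that the two hospitals could print different forms, so that their scores could not be combined. The article does not support this. Both anchors are printed, Data collection describes one dedicated electronic case report form, and Quality control rests with the sponsor hospital's research unit.
- **Proven bias.** A reader might also infer that tolerance is overstated as a matter of fact, because only patients who kept the patch on are counted. The article does not say so. The skin check is tied to the act of removal, not to completing 72 hours, and a nurse taking off the patch of a patient who withdraws would trigger it.
- **Missing data.** The rule means no imputation. It neither forbids a score at withdrawal nor fixes a denominator.
- **Other safeguards.** All adverse events are recorded, so a blister that led to removal could appear there. Time to data loss or end of device service is described with Kaplan-Meier curves, so early loss of signal would be visible.
- **Condensed article.** The full protocol, available on request, may cover scoring at withdrawal.

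These objections stand against any claim of established bias and against the pooling argument. They do not close the gap. Self-removal is outside the wording, withdrawal is described without a score or a reason, and neither safeguard supplies an acceptance score. A Kaplan-Meier curve of signal loss does not separate intolerance from a failed device. The last objection does not touch the scale, which is wrong as printed.

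**Conclusion.** The scale contradiction is certain: five scores under a four-point label, for a stated secondary outcome.

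The second part holds as a risk only. As written, a patient who stops because of the patch may go unscored, and if that happens the error runs towards better tolerance. Its size cannot be known from the article and may be zero. The contrast of 1.8% reported against 6.1% in all patients depends wholly on assuming 2 scored and 5 unscored intolerant patients. Over 0 to 10 unscored patients the gap runs from 0 to 8.6 percentage points. The range does show that, where few intolerable ratings are expected, a handful of unscored removals can outweigh the recorded ones.

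The primary outcome and the sample size are not affected.

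**What to change.** 1. Reconcile label and range with the form in use: either a five-point scale from 0 to 4 or a genuine four-level scale, with a label for every level. Recruitment is under way, so first confirm which form the enrolled patients have completed.
2. Take the skin stage and acceptance score at every patch removal, whatever the time or reason (72 hours, withdrawal, self-removal, imaging), with the patient free to decline.
3. Record whether removal was for discomfort or a skin reaction.
4. Report tolerance over all patients who had a patch applied, counting removal for intolerance as the worst category. Some scores will still be missing because patients may decline, so state how many and show the result with those patients counted first as tolerant and then as intolerant.

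The cost is a corrected form, one field in the electronic case report form and a sentence on the denominator. The tolerance figure may come out less favourable. Treating removal for intolerance as the worst score is an analytic choice, so it should be fixed before the data are examined. Scores not collected at removal are hard to recover afterwards, so an analysis rule alone would not be enough.

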In conclusion, our protocol is specifically aimed to establish whether there is a benefit of remote monitoring using a multiparameter device in the detection of a postoperative complication resulting in an abnormality of one of the major vital signs. This demonstration would encourage the extension of this type of monitoring to hospitalized medical patients and patients at home, which includes many indications: follow-up after discharge, chronic pathology, or acute but not requiring hospitalization.

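### Excluding enrolled patients who need an unplanned scan or MRI probably selects on the outcome and does not fit the 72-hour outcome window

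*Protocol article*

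**What the plan says.** - **Procedure.** After the paragraph on voluntary withdrawal, the article adds that "patients will be excluded during the study if they must undergo an unplanned scan or magnetic resonance imaging during the period of monitoring". It continues: "In this case, the patch will be removed before the radiologic examination". Putting the patch back on is not mentioned.
- **Study population and eligibility criteria.** Imaging already known to be planned is a separate entry criterion: "planned scanner or magnetic resonance imaging during the postoperative course, and pregnancy". That is decided before enrolment and is not at issue.
- **Outcome measures.** The main outcome is at least one episode of MAP below 60 mmHg "during the first 72 hours following a major non-cardiac surgical procedure unless death or hospital discharge occurs sooner". Unplanned imaging is not named as a reason for a shorter window. A secondary outcome is "the postoperative complications that occurred during the monitoring period, as determined by the healthcare team".
- **Statistics.** The main goal is the proportion of patients with severe hypotension, expected to be 8%, estimated to within ±5 points with 114 patients. Nurse and sensor detection are compared per patient in a two-by-two table with kappa and a McNemar test. Missing data are not replaced.
- **Limitations (closing paragraph).** The study is meant to "establish whether there is a benefit of remote monitoring using a multiparameter device in the detection of a postoperative complication".

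**The concern.** An unplanned scan or MRI within three days of major surgery is ordinarily ordered because someone suspects a complication. Excluding a patient for that reason conditions on an event that follows enrolment and is probably associated with both hypotension and complications. The study aims to estimate how often these occur and how well they are detected, so the rule risks removing patients who carry a disproportionate share of the information.

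Taking the patch off for the examination does not by itself require the patient to leave the study. The outcome definition already accepts shortened follow-up for death and discharge. The Limitations section discusses selection from leaving out men with hairy skin, but not this selection, which is closer to the outcome.

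**Working it through.** **Inputs from the article.** Expected prevalence p = 8%, half-width d = 5 points, two-sided alpha 5%, n = 114 (Statistics). Background complication rate, used only as an illustration: "16.8% of patients developed one or more postoperative complications" (Introduction).

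**Inputs not in the article, so assumed.** e = share of enrolled patients excluded for unplanned imaging (2%, 5%, 10%). q = proportion of those excluded who have MAP below 60 mmHg (20% to 40%).

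**1. The plan's own figure.** n = 1.96² × p(1 − p)/d² = 3.8415 × 0.08 × 0.92/0.0025 = 113.09, rounded up to 114. The stated figure is reproduced. The half-width at 114 is 4.98 points, and the expected number of patients with an event is 0.08 × 114 ≈ 9.

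**2. Prevalence among retained patients.** If excluded patients leave the analysis:

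retained prevalence = (p − e·q)/(1 − e), so bias = −e(q − p)/(1 − e).

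The bias is downward whenever q exceeds 8%, and zero when q = 8%.

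| e | q = 20% | q = 30% | q = 40% |
|---|---|---|---|
| 2% | 7.8% | 7.6% | 7.3% |
| 5% | 7.4% | 6.8% | 6.3% |
| 10% | 6.7% | 5.6% | 4.4% |

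Example: e = 5%, q = 30% gives (0.08 − 0.015)/0.95 = 6.8%. The share of events removed is e·q/p: 5% at the mildest corner (0.02 × 0.20/0.08) and 50% at the most severe (0.10 × 0.40/0.08).

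**3. Complication rate.** The same formula applies, with 16.8% as the true rate and a further assumption that 80% of imaged patients have a complication. The retained rate is 15.5%, 13.5% and 9.8% for e = 2%, 5% and 10%.

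**4. Precision.** At 8% prevalence the half-width rises from 4.98 points to 5.03, 5.11 and 5.25 points after losing 2%, 5% and 10%. Keeping 114 analysable patients would need 114/(1 − e) = 117, 120 or 127 enrolled, but that would leave the bias untouched.

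**5. Paired nurse-sensor comparison.** Exclusion removes a patient's nurse result and sensor result together. Whether the discordant pairs lost favour the nurse or the sensor cannot be worked out from the article.

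**6. The milder reading.** If only recording stops and earlier data are kept, a patient whose first episode comes after patch removal has no sensor-detected event. A simple proportion then understates 72-hour prevalence, and the truncation is related to the patient's condition. This is smaller than whole-patient exclusion, but the outcome window does not provide for it.

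**The case against.** The strongest reply is that the article never says data recorded before patch removal are discarded. The sentence follows the withdrawal paragraph and can be read as ending participation, not as deleting the record. Analysis sets are commonly left to the full protocol or analysis plan, and neither is shown. Parts of the Statistics section suit partial records: Kaplan-Meier curves are planned for end of device service and for first complication. This stands as a limit on certainty. A reader might infer that all valid earlier data are thrown away, but the article does not establish that. It does fix an exclusion rule tied to a post-enrolment event and an outcome window that does not allow for it, so the point is not merely about omitted detail.

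A reader might also infer a large bias. For example, suppose half of the 16.8% with complications are imaged and 30% of those are hypotensive. Then 0.168 × 0.5 = 8.4% are excluded, 0.084 × 0.30/0.08 = 31.5% of events are lost, and 8% becomes (0.08 − 0.0252)/0.916 = 6.0%. The arithmetic is right, but the article gives no imaging rate and no hypotension rate in imaged patients. It also does not tie the 16.8% to the first 72 hours or to patients like these. At 2% excluded, the shift is under one point against a planned ±5.

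Two further readings go too far. Precision is not seriously harmed (step 4). Nor can the nurse-sensor comparison be called biased in a given direction (step 5).

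**Conclusion.** The point holds in limited form. The exclusion rule is triggered by an event likely to be linked to complications, and it conflicts with an outcome window that only death or discharge shortens. If excluded patients leave the analysis, hypotension prevalence and the complication rate are expected to be too low. For a true 8%, the estimate would be 7.8-7.3%, 7.4-6.3% or 6.7-4.4% at 2%, 5% or 10% excluded. This rests on an assumed 20-40% event rate among those excluded, and the bias vanishes if imaging is unrelated to hypotension. If exclusion only stops recording, the problem reduces to informative truncation of the sensor window. This should be fixed. The article does not establish the frequent imaging and whole-record exclusion that would make it critical.

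**What to change.** Leave imaging and patch removal exactly as written. Replace the exclusion with wording such as: *Patients who undergo unplanned imaging remain in the analysis set. Sensor data are used up to patch removal; nurse observations and complications are collected to 72 h.* Then:

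- Restrict the paired comparison (two-by-two table, kappa, McNemar) to the period when the patch was worn. Otherwise nurses would have a longer window than the sensor in these patients.
- Estimate sensor-detected hypotension with all enrolled patients in the denominator. Support it with a Kaplan-Meier estimate of time to first episode, censored at patch removal, and note that this censoring may be informative.
- Report the number, timing and reasons for removals, with a sensitivity analysis in patients with full 72 h recording.
- Retain the sensor data of patients already excluded, where consent allows. Recruitment is ongoing, and Data collection permits sensor data to be deleted during the study.
- Amend the outcome window so that it states how patch removal for imaging is handled.

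The cost is a one-paragraph amendment and a short analysis rule. Nurse and complication data are already charted routinely. The downside is some shorter sensor records.
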